### Integrated multi-omics analysis

3.5.

Multi-omics data from patients with well-defined phenotypes (e.g., Brighton level 1 TTS/VITT) and controls will be analyzed using data integration approaches such as MultiOmics Factors Analysis (MOFA) and Data Integration Analysis for Biomarker Discovery using Latent Components (DIABLO) as previously described [84,85]. MOFA is a computational method used to integrate and analyze multi-omics datasets which distinguishes between patterns that are shared across different omics layers and those that are specific to individual layers [84]. DIABLO identifies key drivers associated with the response variable of interest across all input data matrices jointly. Cross-validation will determine the optimal model hyperparameters (number of components, features per component) and estimate the model’s ability to generalize to new data. Selected model features will undergo pathway over-representation analysis against the Reactome pathways database (via MSigDB) and blood transcriptional module (BTM) annotated gene set libraries, with *p*-values adjusted to control false discovery rate (FDR).

Multi-omics data will be compared within groups over time (e.g., myocarditis/TTS/VITT onset vs post-recovery) and between cases and controls to identify differences in basal levels of analytes in cases (using baseline samples: pre-vaccination, post-recovery/ ≥3 months postvaccination), as well as at time of myocarditis/TTS/VITT diagnosis (and similar timepoints post-vaccination in controls). Analyte levels in blood/plasma will also be compared to normal ranges in adults where available. Two-way comparisons will be performed between cases and healthy controls vs cases and controls with non-vaccine associated myocarditis or HIT.

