#### Case-control matching

2.4.3.

Cases will be matched to healthy controls, recruited through observational vaccine studies and other approaches, who received the same vaccine platform and, where feasible, the same product (e.g., BNT162b2 or mRNA-1273) and did not develop an AEFI. Samples from these controls will be matched to cases at a ratio of at least 1:1 and ideally 3:1 for multi-omics analysis by age group, biological sex, vaccine type, and ancestry.

Cases may also be frequency matched to controls with a non-vaccine-associated TTS/VITT-like condition (e.g., heparin-induced thrombocytopenia [HIT]) or non-vaccine-associated myocarditis or pericarditis, who meet Brighton criteria and have samples collected and stored at the time of their clinical presentation. Matching will be done by age (±5 years), biological sex, ancestry (where possible), and vaccine received (for healthy controls).

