#### Sample collection and processing

2.4.4.

Both cases and controls will undergo data and sample collection for multi-omics analyses, including transcriptomics, proteomics, and metabolomics using a standardized protocol. Samples will be captured as close to the onset of an AE as possible, up to 12 weeks after the event, with follow-up samples collected as needed. Participants will also be invited to consent to saliva or blood sampling for DNA extraction and genotyping under the GVDN genomics protocol.

Sample collection for cases and controls will be conducted using retrospective residual clinical samples or prospectively at selected sites. At each timepoint (see Table 1), peripheral blood (5–15 ml) will be collected according to protocol. Where processing facilities are available, whole blood (20–30 ml) will be collected for PBMC isolation. Additional sample types, including serum, may be collected according to site-specific or study-specific protocols (refer to INSIS Study SOP in supplementary file 1). Samples for multi-omics analysis will be stored at the participating site until they are ready to be shipped on dry ice or liquid nitrogen to an INSIS laboratory with biobanking facilities, such as the Precision Vaccines Program (PVP), where they will be stored at −80 °C until analysis (Fig. 2). As of May 15, 2025, 7 sites have entered data for 154 cases and 110 controls into the INSIS REDCap database, with >1100 samples (including serum, plasma, PBMC, and saliva) recorded in the INSIS REDCap database. Additionally, > 1600 sample aliquots have been entered into the Laboratory Data Management System (LDMS) [41] sample management system. These numbers will continue to increase as sites enter their data into the INSIS REDCap and LDMS databases.

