### Data harmonization framework

3.2.

Harmonized procedural and data processing pipelines across assays are coordinated via the INSIS Data Management Working Group (DMWG) with support from the DMAC. As the cohort is recruited, plans will address missing clinical data and samples and appropriately randomize samples for each assay type to eliminate selection bias and evenly distribute confounding variables. Power calculations will be conducted to ensure that the study is adequately powered to detect significant differences or associations in the data, accounting for potential variability and expected effect sizes. Standardized metadata templates and controlled vocabularies will be applied to ensure data interoperability across sites and assay platforms. As part of our quality control and assurance measures, we recognize that self-reported demographic variables such as gender and race may vary in consistency across study sites. We will incorporate both self-reported and where available, biologically inferred variables (e.g. genetic ancestry, sex chromosome-linked gene expression) during analysis.

Once the data are uploaded to the INSIS study database, DMAC data managers and biostatisticians will coordinate and verify quality control (QC) processes for data collected/generated at clinical sites and Core Labs. They will also perform additional quality assurance (QA) to maintain the highest possible accuracy of clinical, immunologic, and systems biology data before reporting and analysis in the centralized cloud computing system (Fig. 4).

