### Analysis of clinical features and outcomes

3.4.

Clinical features, results of investigations, other exposures or risk factors, and outcomes of the AEFI will be compared within each subgroup by vaccine product, age, biological sex, self-reported gender, and race. Examples of analysis will include multivariable regression analysis which will identify demographic and clinical factors associated with Brighton Collaboration case definition-confirmed TTS/VITT, myocarditis, and pericarditis in cases versus healthy controls. Additionally, we plan to compare factors related to post-vaccination versus non-vaccine associated myocarditis and TTS/VITT versus HIT/VITT-like non-vaccine associated syndromes. Similar approaches will be employed for new AEFIs that emerge as safety signals.

With sufficient sample size, some samples may be used for discovery cohorts and others for replication, with one network (e.g., INSIS) leading an omics discovery analysis and providing samples for the replication of another network’s analyses. Similar sample size and matching approaches will be used for new AEFI targets. INSIS will partner with GVDN to recruit cases and controls for genomics analysis in GVDN-led studies.

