* Participants may be included if multi-OMICs samples are available from only 1 timepoint but 2 or more timepoints are preferred within these approximate timeframes (preferably an acute sample and follow up sample). In some cases an early follow up sample and late follow up sample (e.g., 3 and > 6 months) will be acceptable. A maximum of 90 ml of blood will be drawn on children <16 years of age.

† At time of first specialist assessment (e.g., cardiology, special immunization clinic).

‡ If not consented at presentation, consent will be obtained at time of specialist assessment for retrieval of residual serum/plasma from initial presentation.

** Aim for 3–7 days post-vaccination for controls matched to myocarditis cases; 5–42 days post-vaccination for controls matched to VITT cases, longer timeframes may be appropriate for additional AEFI of interest.

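### Section 3.5 assigns both the tuning of the DIABLO model and the estimate of its performance to cross-validation without separating them; read as written, the reported performance is optimistic

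*Protocol article*

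**What the plan says.** Section 3.5 (Integrated multi-omics analysis) names MOFA and DIABLO as integration methods. It then says: "Cross-validation will determine the optimal model hyperparameters (number of components, features per component) and estimate the model’s ability to generalize to new data". The hyperparameters listed are those of the supervised method, DIABLO. No nesting, outer loop or held-out set is mentioned, and nothing says that the two tasks share folds.

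The data entering the model are described as "Multi-omics data from patients with well-defined phenotypes (e.g., Brighton level 1 TTS/VITT) and controls", which is a subset of the cohort. The cohort to May 2025 is given in section 2.4.4: "7 sites have entered data for 154 cases and 110 controls into the INSIS REDCap database". It is still growing, and no split by adverse event is shown. Sections 2.4.1 and 2.4.2 divide the cases further: myocarditis versus pericarditis alone, and PF4-positive VITT versus other TTS. Power calculations are deferred in section 3.2.

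Two features of the design make samples dependent. On matching, section 2.4.3 says: "Samples from these controls will be matched to cases at a ratio of at least 1:1 and ideally 3:1". On repeated sampling, the Table 1 footnotes say: "Participants may be included if multi-OMICs samples are available from only 1 timepoint but 2 or more timepoints are preferred".

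Independent confirmation appears only in section 3.4, as a possibility: "With sufficient sample size, some samples may be used for discovery cohorts and others for replication".

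**The concern.** When many settings are compared by cross-validation and the best is kept, its cross-validated error is the minimum of many noisy estimates. That minimum lies below the error the chosen model would have on new people. It is a legitimate tool for choosing a setting but a biased estimate of performance. Section 3.5 gives cross-validation both jobs and presents the second as a statement about new data.

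The bias is largest with few participants, many features and a grid that spans several omics blocks, which is the setting for a single rare adverse event. Because replication is conditional and not tied to the DIABLO estimate, the optimistic figure may be the only one published. According to the Fig. 2 legend, the intended outputs are biomarkers that predict or accompany these events and inform vaccine development and personalised vaccination. A panel that looks modestly predictive but is noise would mislead that work.

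**Working it through.** The article states no sample size, power or performance for this analysis, so there is no figure of its own to reproduce. The check is whether reusing the tuning cross-validation inflates performance when there is no signal at all.

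**Inputs from the article:** tuning covers the number of components and the features per component (section 3.5); 154 cases and 110 controls, 264 in all (section 2.4.4); at least one and ideally three controls per case (section 2.4.3).

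**Assumptions (not in the article):** group sizes per adverse event, number of blocks and features, grid, 5-fold cross-validation, and simplified DIABLO-like classifiers.

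**Formulas.** Balanced error: BER = ½ × (missed cases / n₁ + misclassified controls / n₀). With no signal, the expected BER of every setting g is 0.50, but E[min over g of BER(g)] < 0.50. Optimism = mean nested BER − mean minimum BER.

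**Simulation A.** Three noise blocks of 200 features; sparse PLS-DA per block, averaged over blocks; feature selection inside each fold; four feature counts per block (4³ = 64 combinations) × 1 to 3 components = 192 settings; 300 replicates per size (269 for the pooled size).

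| Cases + controls | Fixed setting, BER | Tuned and reported from same CV, BER | Nested CV, BER | Optimism | AUC ≥ 0.65 on noise: same CV / nested |
|---|---|---|---|---|---|
| 15 + 15 | 0.492 | 0.337 | 0.489 | 0.152 | 49% / 21% |
| 25 + 25 | 0.501 | 0.378 | 0.503 | 0.125 | 38% / 10% |
| 50 + 50 | 0.498 | 0.410 | 0.502 | 0.092 | 18% / 2% |
| 25 + 75 | 0.500 | 0.397 | 0.499 | 0.102 | 26% / 5% |
| 154 + 110 | 0.502 | 0.445 | 0.502 | 0.057 | 3% / 0% |

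Monte Carlo standard errors of the tuned and nested means are 0.002 to 0.007. The same-CV AUC is the largest over the grid; the nested AUC is for settings chosen on BER. Mean AUC with the same CV is 0.650, 0.609, 0.581, 0.592 and 0.549 in row order; with nesting it is 0.495 to 0.512.

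**Simulation B.** Different assumptions: blocks of 1000, 800 and 123 features; 125 feature-count combinations; t-statistic selection inside folds with diagonal discriminant scores; 150 replicates. The tuned BER averages 0.36 at 25 per group (5th percentile 0.24) and 0.41 at 50 per group (5th percentile 0.32). The two simulations agree closely.

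**Scale check.** For one setting, the approximate standard error of BER at 0.50 is ½ × √(0.25/n₁ + 0.25/n₀).
- 15 + 15: SE 0.091; (0.50 − 0.337)/0.091 = 1.8.
- 25 + 25: SE 0.071; (0.50 − 0.378)/0.071 = 1.7.
- 50 + 50: SE 0.050; (0.50 − 0.410)/0.050 = 1.8.
- 25 + 75: SE 0.058; (0.50 − 0.397)/0.058 = 1.8.
- 154 + 110: SE 0.031; (0.50 − 0.445)/0.031 = 1.8.

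Under these assumptions the tuned error sits nearly two standard errors below the truth at every size, so the bias shrinks only with the square root of the sample size.

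**Conditional check on repeated samples.** With two samples per person (assumed within-person correlation 0.5 to 0.7, 80 replicates) and folds drawn over samples, the tuned BER on noise falls to 0.22 to 0.17. With folds drawn over participants that leakage disappears and only tuning optimism remains (0.42 to 0.44). The article does not say how folds are drawn.

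**The case against.** The strongest reply is that shared folds are inferred. Nested cross-validation also tunes and also estimates performance, and the sentence could be a short description of it. The methods are said to follow published descriptions, and an article may leave loop structure to a fuller protocol or an analysis plan that is not shown. This stands in part: the article cannot be said to prescribe the flawed procedure. But it does more than stay silent, since it gives both tasks to cross-validation and labels the result as performance on new data.

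A second reply is that the size depends on unstated numbers. This also stands. With all 264 participants pooled, the noise AUC averages about 0.55 and would hardly pass for a working panel. A larger grid would raise the bias; repeated cross-validation or a one-standard-error rule would lower it. Pooling all events is not the described analysis, however, so single-event groups will be smaller.

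A third reply is that DIABLO is one of several tools in an observational mechanism study, and that its selected features go on to pathway analysis with false discovery control. That control concerns pathways; it does not correct the classifier's reported accuracy.

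Two stronger readings are tempting and not supported. A reader might infer from the preference for repeated samples that noise could show an accuracy of about 80%. That needs several samples per person in one classifier and folds drawn over samples. The article states neither, and section 3.5 describes case-control comparisons by timepoint, which can use one sample per person. A reader might also move on to population predictive values. Section 3.5 plans none, and the Introduction gives numerical incidence for VITT only, so that is a separate matter.

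**Conclusion.** The point holds in limited form. Section 3.5 does not separate tuning from performance estimation, and no independent estimate is guaranteed. If the sentence is carried out on its natural reading, the performance reported for the selected DIABLO model is optimistic. Under the assumed grids, blocks and 5-fold scheme, balanced error is flattered by about 0.09 to 0.15 at 15 to 50 cases and by about 0.06 at the full pooled size. Nested cross-validation removes this bias. It does not remove imprecision: at 15 + 15 noise still reaches an AUC of 0.65 in 21% of runs, close to the 18% seen with a fixed, untuned setting. The figures illustrate the mechanism and do not predict this study's bias, because its group sizes and grid are not stated.

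**What to change.** Replace the sentence in section 3.5 with wording to this effect: *Hyperparameters are tuned in an inner loop. Performance is reported only from the outer folds of a nested cross-validation, or from a replication set locked before model fitting. All samples of a participant, and of an individually matched set where one exists, stay in the same fold. Normalisation, imputation, batch correction and other data-driven preprocessing are fitted within training folds.*

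The matched-set rule cannot apply to disease controls who are only frequency matched, because they form no individual sets. A label-permutation check is a useful option at small group sizes, where a nested estimate is unbiased but still variable.

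The change needs no new data or samples. It costs extra computing time, and the reported accuracy will be less favourable. It is best made before any model is fitted.

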#### Myocarditis/pericarditis

2.4.1.

The Brighton Collaboration case definitions ([37], [38])will be used for both post-vaccine and non-vaccine-associated cases of myocarditis and pericarditis. These events will be categorized into two groups for analysis: myocarditis (with or without signs of pericarditis) and pericarditis without myocarditis. Clinical and demographic features, diagnostic testing results, and multi-omics datasets for these cases will be compared to healthy controls and controls with non-vaccine-associated myocarditis.

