#### Thrombosis with Thrombocytopenia Syndrome (TTS)/Vaccine-Induced Immune Thrombocytopenia and Thrombosis (VITT)

2.4.2.

The Brighton Collaboration case definition will be applied to both post-vaccine and non-vaccine-associated cases of TTS/VITT [39,40]. This allows differentiation between vaccine-induced TTS/VITT and non-vaccine associated TTS cases. Clinical and demographic features, diagnostic testing results, and multi-omics datasets will be analyzed for PF4+ VITT cases and TTS not meeting VITT criteria, versus healthy vaccinated controls and controls with non-vaccine-associated TTS/VITT-like conditions [39].

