**Fig. 2. F2:**
[figure not shown]
The International Network of Special Immunization Services (INSIS) approach to defining biomarkers of vaccine-associated adverse events. A) AEFI cases and controls are recruited. B) Cases and controls undergo standard assessment, data and sample are collected at INSIS clinical assessment centers. C) Data are transferred to the INSIS central database, and samples are processed at INSIS laboratories for multi-OMICs. D) Integration and analysis of clinical and biological data. E) Biomarkers that predict or correspond to AEFIs will be identified. F) Results will inform vaccine development and personalized vaccination strategies. Abbreviation: AEFI, adverse event following immunization.

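### Section 3.5 interprets the features selected by the integration model without any check of whether the same features would be selected again

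*Protocol article*

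**What the plan says.** Section 3.5 (Integrated multi-omics analysis) names MOFA and DIABLO as examples of integration methods. Cross-validation has two tasks there: to choose how many components, and how many features on each, the model keeps, and to estimate how well the model predicts in new data. The next step is interpretation: "Selected model features will undergo pathway over-representation analysis against the Reactome pathways database" and blood transcriptional modules, with pathway p-values adjusted for FDR. The Fig. 2 caption gives the intended product: "Biomarkers that predict or correspond to AEFIs will be identified".

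On numbers, Section 2.4.4 reports that by 15 May 2025 "7 sites have entered data for 154 cases and 110 controls", pooled over conditions, and adds: "These numbers will continue to increase as sites enter their data into the INSIS REDCap and LDMS databases". Section 2.4.3 wants healthy-control samples "matched to cases at a ratio of at least 1:1 and ideally 3:1 for multi-omics analysis". Section 2.4.1 sets out two cardiac groups: "These events will be categorized into two groups for analysis: myocarditis (with or without signs of pericarditis) and pericarditis without myocarditis". Section 2.4.2 separates "PF4+ VITT cases and TTS not meeting VITT criteria". Section 3.4 allows some samples to be kept for replication if numbers suffice, but does not commit to it. The one firm validation step, in Section 2.11.2, is for GWAS variants and not for multi-omics features.

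**The concern.** Sparse selection from thousands of correlated analytes is sensitive to which participants are in the sample. Two quite different feature lists can predict equally well, so a good cross-validated error rate is no evidence that the list would be reproduced. Pathway FDR does not help either, because it takes the list as given and tests only how the listed features fall into gene sets. The over-representation test also treats features as if they were drawn independently, whereas correlated features enter the list together.

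At stake is how the output can be read. A feature selected in nearly every refit and one selected by chance would be reported, and would enter the pathway test, with the same weight.

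**Working it through.** **No figure to reproduce.** The article gives no sample size, effect size or error rate for this analysis. The check is a simulation on stated assumptions.

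**Cases per condition.** Assuming an even split of the 154 cases: 154/2 = 77, 154/3 = 51, 154/4 = 38.5. The four-way split corresponds to the groups in Sections 2.4.1 and 2.4.2. Restriction to well-defined phenotypes, for which Section 3.5 gives Brighton level 1 as an example, would lower these figures. Continued recruitment would raise them. A range of 25 to 50 cases, with 1 or 3 controls per case, was therefore examined.

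**Assumptions, none from the article.** 5,000 features in 100 sets of 50. Five sets are active, with half their features shifted, so 5 × 25 = 125 features are true. Individual effects are 0.5 to 1.5 times a mean effect d (in SD). Correlation within sets is 0.3. Each setting has 60 pairs of independent samples.

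**Steps.**
1. Rank features by |mean in cases − mean in controls| / pooled SD and keep the top 50. With a binary outcome and scaled data, this is the selection made by the first component of a sparse PLS-DA, a one-block stand-in for DIABLO.
2. Feature recurrence = (features in both lists) / 50. By chance alone this is 50/5,000 = 1%.
3. For each set, take a hypergeometric p-value for the number of its features in the list (expected by chance: 50 × 50/5,000 = 0.5), then apply Benjamini-Hochberg at 5% over the 100 sets.
4. Pathway recurrence = share of significant sets in sample 1 that are also significant in sample 2.

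**Results, correlation 0.3** (feature recurrence / true share of the list / pathway recurrence, in %):

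| Cases v controls | d = 0.4 | d = 0.6 | d = 0.8 | d = 1.2 |
|---|---|---|---|---|
| 25 v 25 | 5 / 29 / 25 | 20 / 58 / 56 | 43 / 84 / 88 | 67 / 100 / 98 |
| 25 v 75 | 10 / 41 / 40 | 39 / 81 / 85 | 59 / 97 / 96 | 72 / 100 / 98 |
| 50 v 50 | 19 / 58 / 62 | 53 / 92 / 94 | 65 / 100 / 95 | 74 / 100 / 99 |
| 50 v 150 | 36 / 78 / 82 | 65 / 99 / 96 | 71 / 100 / 97 | 80 / 100 / 100 |

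The share of features that do not recur is 100 minus the first figure: 64% to 95% at d = 0.4 and 35% to 80% at d = 0.6. Failure to recur does not always mean a false feature. With 125 true features competing for 50 places, the list can change while remaining almost wholly true, as at 50 v 50 and d = 0.8.

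**No true effect (d = 0).** Feature recurrence is 1%. With correlation 0.3, 1.6 to 2.0 sets per analysis pass 5% FDR and 0% to 3% of them recur. With correlation 0, only 0 to 0.04 sets pass. Correlation alone therefore produces the significant pathways.

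**What selection frequency adds.** At 38 v 38 and d = 0.5, on the same assumptions, 61% of single-fit features were true, against 80% of features selected in at least 80% of refits.

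**What it would cost to make the stable list the main pathway analysis.** True pathways found, out of 5, at d = 0.5: from 3.25 down to 1.40 at 38 v 38, and from 3.80 down to 2.30 at 38 v 114. A second run gave 3.11 down to 1.41 and 3.95 down to 2.29. In that run false pathways fell only from 0.44 to 0.05 and from 0.21 to 0.01.

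**The case against.** The strongest reply is that this is a gap in a condensed article, and that selection frequencies belong in an analysis plan that is not shown. That has force and limits how hard the point can be pressed. But Section 3.5 does spell out the tuning, the pathway libraries and the FDR step, so the sequence it publishes can be reviewed as written. A fair further point is that, with no signal at all, poor cross-validated prediction could warn the analysts.

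Several stronger readings are tempting and are not supported:
- A reader might infer that one DIABLO fit leads directly to biomarker claims. The text names MOFA as well, offers both as examples, plans direct analyte comparisons over time and between groups, and allows for replication. The Fig. 2 caption states an overall aim and does not tie biomarkers to one fit.
- A reader might divide 154 cases and 110 controls by four and take 38 v 27 as the design. That is below the 1:1 minimum in Section 2.4.3, ignores continuing recruitment, and assumes that conditions cannot share controls.
- A reader might conclude that most reported pathways would not recur. At 50 v 50, 94% or more recur from d = 0.6, because exchanging one correlated feature for another often leaves the pathway unchanged.
- A reader might suppose that unstable features would determine the in vitro work. Section 2.13 fixes those test conditions in advance.
- A reader might assume that tuning already supplies the refits needed. Repeated cross-validation is not mentioned, and tuning fits vary the very settings that must be held fixed.

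**Conclusion.** The point holds in a limited form. As published, Section 3.5 moves from tuning and prediction error to interpretation of the selected features with no measure of whether they would be selected again, and pathway FDR does not supply one. On the assumptions above, with 25 to 50 cases and mean effects of 0.4 to 0.6 SD, roughly a third to nearly all of the selected features would not recur. Where there is no effect, correlated features can still give one or two FDR-significant pathways. Features are reasonably stable at large effects: at 50 v 50, 65% or more recur from d = 0.8. Pathways are fragile mainly with about 25 cases, small effects or no signal.

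The simulation is a one-block proxy in which the gene sets coincide with the correlated blocks, and neither the numbers per condition nor the effect sizes are in the article. The percentages illustrate the size of the problem and do not predict this study's results. This is a worthwhile, low-cost improvement and not a flaw that invalidates the analysis.

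**What to change.** In Section 3.5, after tuning:
1. Refit the final model at the chosen settings on repeated subsamples or by repeated cross-validation.
2. Report the selection frequency of every named feature and the recurrence of every reported pathway across the refits.
3. Describe a feature as a candidate biomarker only when its frequency is shown, and mark low-frequency features as unstable.
4. Keep the full selected list for the main pathway analysis. Add, as a sensitivity analysis, the same test restricted to frequently selected features, for example those in at least 80% of refits.

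The 80% figure is a convention. In the 38 v 38 example one in five features above it was still false (100% − 80%), so selection frequency does not replace replication. The restricted list should not become the main pathway analysis, given the loss of true pathways shown above. No new participants or samples are needed. The cost is computing time and more cautious wording for unstable features.
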